## Abstract

**Background and Objectives:**

Almost one third of cancer patients in the United States will develop brain metastases on an annual basis. Surgical resection is indicated in the setting of brain metastases for reasons, such as maximizing local control in select patients, decompression of mass effect, and/or tissue diagnosis. The current standard of care following resection of a brain metastasis has shifted from whole brain radiation therapy to post-operative stereotactic radiosurgery (SRS). However, there is a significant rate of local recurrence within one year of postoperative SRS. Emerging retrospective and prospective data suggest pre-operative SRS is a safe and potentially effective treatment paradigm for surgical brain metastases. This trial intends to determine, for patients with an indication for resection of a brain metastasis, whether there is an increase in the time to a composite endpoint of adverse outcomes; including the first occurrence of either: local recurrence, leptomeningeal disease, or symptomatic radiation brain necrosis - in patients who receive pre-operative SRS as compared to patients who receive post-operative SRS.

**Methods:**

This randomized phase III clinical trial compares pre-operative with post-operative SRS for brain metastases. A dynamic random allocation procedure will allocate an equal number of patients to each arm: pre-operative SRS followed by surgery or surgery followed by post-operative SRS.

**Expected outcomes:**

If pre-operative SRS improves outcomes relative to post-operative SRS, this will establish pre-operative SRS as superior. If post-operative SRS proves superior to pre-operative SRS, it will remain a standard of care and halt the increasing utilization of pre-operative SRS. If there is no difference in pre- versus post-operative SRS, then pre-operative SRS may still be preferred, given patient convenience and the potential for a condensed timeline.

**Discussion:**

Emerging retrospective and prospective data have demonstrated some benefits of pre-op SRS vs. post-op SRS. This study will show whether there is an increase in the time to the composite endpoint. Additionally, the study will compare overall survival; patient-reported outcomes; morbidity; completion of planned therapies; time to systemic therapy; time to regional progression; time to CNS progression; time to subsequent treatment; rate of radiation necrosis; rate of local recurrence; and rate of leptomeningeal disease.

**Trial registration number:**

NCT03750227 (Registration date: 21/11/2018).

## Rationale and background information

Approximately 175,000 patients in the United States yearly, or 10–30% of cancer patients, develop brain metastases [1–5]. The current standard of care for brain metastasis is post-operative stereotactic radiosurgery (SRS) [6–12]. However, 28% of patients undergoing post-operative SRS after resectioning of one, two, or three metastases recurred locally within one year [10]. Opportunities for improvement in local control and clinical outcomes therefore remain. Dose escalation may improve local control but at the expense of toxicity including radiation-induced necrosis. Within the field of radiation oncology, there has been an increase in the utilization of neoadjuvant therapy, including but not limited to rectal, pancreatic, and esophageal cancers as well as sarcoma [13]. This strategy of neoadjuvant radiation has been gaining interest in the setting of brain metastases. Neoadjuvant SRS prior to surgical resection of brain metastases has a number of potential advantages over adjuvant SRS, including 1) a better-defined target volume delineation as opposed to a post-operative bed; 2) the potential for a “sterilization” effect prior to surgery, and therefore, the potential to decrease the rate of ‘seeding’ of viable tumor cells that could contribute to post-operative regional or leptomeningeal disease; 3) rates of radiation necrosis may be decreased with pre-operative SRS, given the potential to resect irradiated tissue surrounding the resected metastasis involving non-eloquent regions. Disadvantages include 1) the lack of pathologic confirmation prior to SRS: 2) being non-compatible with emergent surgical indications (uncommon), the potential need to decrease margin dose for large as-yet unresected lesions, and 3) the potential risk of wound healing complications operating after recent radiation [13]. Emerging retrospective and prospective data have demonstrated that some of the theoretical benefits may hold true [14–18]. Pre-operative SRS appears to be a safe and potentially effective treatment paradigm for surgical brain metastases. We present our ongoing randomized phase III clinical trial protocol comparing pre-operative with post-operative SRS for brain metastases.

## Study goals and objectives

### Primary goals

To determine for patients with brain metastases meeting the inclusion criteria, whether there is an increase in the time to a composite endpoint of adverse outcomes, including the first occurrence of either: local recurrence, leptomeningeal disease, or symptomatic radiation brain necrosis; in patients who receive SRS prior to surgery as compared to patients who receive surgery prior to SRS.

Radionecrosis will be defined radiologically based on MRI. Dynamic susceptibility weighted (DSC) imaging is preferred at each followup. Radionecrosis will be determined qualitatively by radiology per standard institutional clinical assessment. General guidelines are consistent with Alliance A221208 and other institutional trials. When radionecrosis is questionable, or uncertainty is documented, blinded central review will be performed. Relative cerebral blood volume (rCBV) in the enhancing lesion, relative to normal appearing white matter may be used, with a ratio of < 1.5 suggesting necrosis. For conventional MR, a lesion quotient, defined as the T2-weighted hypointense lesion over the maximum axial cross-sectional area of the contrast-enhancing lesion defined on the T1-weighted post-gadolinium sequence on a comparable axial slice can be considered in assessment, and rating of necrosis with a suggested quotient of < 0.3. This metric has accuracy limitations and may be more useful to rule in recurrent tumor than to rule out recurrent tumor.

Leptomeningeal disease (LMD) will be determined based on CSF cytology when available as obtained per clinical indication. Positive CSF will be classified as diffuse LMD. LMD will otherwise represent a radiologic diagnosis, per radiology, per standard institutional assessment and care. Features as below will be considered: Leptomeningeal enhancement including nodules, diffuse enhancement, and including distant sites as well as spine. Spinal imaging will be performed as clinically indicated and lumbar puncture as above will be obtained per clinical care and institutional standard. LMD will be further classified as local versus diffuse. Local: within 3 cm of the surgical bed in the absence of diffuse. LMD Diffuse: Any LMD away from surgical bed (> 3 cm) and/or positive CSF.

### Secondary goals

Overall Survival: to determine for patients with brain metastases whether there is improved overall survival for patients who receive SRS prior to surgery compared to patients who receive SRS after surgery.Patient-Reported Outcomes: to determine for patients with brain metastases whether there is improved patient-reported outcomes, including quality of life for patients who receive SRS prior to surgery compared to patients who receive SRS after surgery.Neurosurgical Morbidity: to determine if preoperative SRS increases surgical morbidity rates including postoperative complications such as wound infection, need for longer hospital stays, or readmission compared to a surgery-first approach for resectable brain metastases.Completion of Planned Therapies: to determine for patients with brain metastases whether there is a higher completion rate of planned therapies for patients who receive SRS prior to surgery than patients who receive surgery prior to SRS.Time to Systemic Therapy: to determine for patients with brain metastases whether there is a shorter time to initiation or re-initiation of systemic therapy with pre-operative versus post-operative SRS.Time to Regional Progression, CNS Progression, and time to subsequent treatment, including WBRT: to determine for patients treated with pre-operative SRS whether there is a longer interval to regional progression, any CNS progression, or need for subsequent intracranial treatment compared to patients receiving post-operative SRS.Rate of Radiation Necrosis: to determine for patients with pre-operative as compared to post-operative radiation whether there is a decreased rate of radiation necrosis, including asymptomatic and symptomatic radiation necrosis.Rate of Local Recurrence: to determine for patients with pre-operative as compared to post-operative radiation whether there is a decreased rate of local recurrence.Rate of Leptomeningeal Disease: to determine for patients with pre-operative as compared to post-operative radiation whether there is a decreased rate of leptomeningeal disease.

### Correlative research

To determine the genetic and molecular alterations of brain metastases seen after radiation versus in the resection setting alone, including early radiobiologic changes in tissue treated with SRS 24 to 48 h prior, and to investigate the detection rate of corresponding circulating DNA and/or inflammatory markers in peripheral specimens.To investigate the usefulness of biomarkers and response to radiation in predicting local control and outcomes.

### Study design

This multicentric randomized phase III trial for patients with one to 10 brain metastases.

#### Study populations

The study population inclusion and exclusion criteria are described in Table 1.

**Table 1 Tab1:** Study Inclusion/Exclusion criteria

**Inclusion criteria**
Age ≥ 18 years
Histological or cytological confirmation of solid tumor malignancy and/or clinical history of known or suspected metastatic disease with an intraparenchymal brain tumor consistent with brain metastasis based on clinical and radiologic findings
Clinical indication for surgical resection of one brain metastasis based on neurosurgery recommendation and patient deemed a surgical candidate
Clinical indication and plan for stereotactic radiosurgery to all known brain lesions requiring treatment (< 10 metastases)
ECOG Performance Status ≤ 2
Provide written informed consent or have a Legally Authorized Representative who is responsible for the care and well-being of the potential study participant, provide consent
Willing to return to enrolling institution for follow-up (during the Active Monitoring Phase of the study) or agreement to complete pre-specified MRI series and follow-up visits according to the study timeline (see Methodology section) mailing in digital copies of images as well as clinical notes
**Exclusion criteria**
Pregnant women
Nursing women
Men or women of childbearing potential who are unwilling to employ adequate contraception
Co-morbid systemic illnesses or other severe concurrent disease which, in the judgment of the investigator, would make the patient inappropriate for entry into this study or interfere significantly with the proper assessment of safety and toxicity of the prescribed regimens
Immunocompromised patients and patients known to be HIV positive and currently receiving antiretroviral therapy. NOTE: Patients known to be HIV positive, but without clinical evidence of an immunocompromised state, are eligible for this trial
Uncontrolled intercurrent illness including, but not limited to, ongoing or active infection, symptomatic congestive heart failure, unstable angina pectoris, cardiac arrhythmia, or psychiatric illness/social situations that would limit compliance with study requirements
Prior open neurosurgery for malignancy
Known or clinically suspected primary germ cell tumor, small cell carcinoma, or lymphoma
History of Whole Brain Radiation Therapy (WBRT)
Known allergy to gadolinium, pacemaker, or other contraindication such as metal implant that is not safe for MRI. Patients with MRI-compatible implants including MRI compatible pacemakers are eligible
Leptomeningeal metastasis/disease
A brain metastasis that is located ≤ 5 mm of the optic chiasm
Any brain metastasis > 5 cm in size
> 10 brain metastases
Indication for surgical resection of ≥ 2 brain metastases
Indication for long-term (anticipated greater than 4 weeks) 4 mg dexamethasone equivalent of steroids or bevacizumab

## Methodology

Upon enrolment, patients will be randomly assigned to one of the two arms: Arm A – pre-operative SRS followed by surgery or Arm B – surgery followed by post-operative SRS. A dynamic allocation procedure will allocate an equal number of patients to each arm. This procedure will balance the marginal distributions of the stratification factors between arms. Stratification factors include:Age: less than 60 versus those 60 or olderNumber of brain metastases: 1 vs. 2–4 vs. 5–10Tumor Size: Planned resection of metastasis < 3.0 cm vs. > 3.0 cm (but < 5.0 cm)Primary Malignancy: Lung vs. Radioresistant (melanoma, renal cell carcinoma, sarcoma) vs. OtherDural Contact: Yes, versus No, with dural contact defined radiologically as suspicion of loss of a plane between the tumor and dura or within 1 mm.RT modality: SRS planned as LINAC vs. Gamma knife

### Randomization

The balancing algorithm that we will use is a dynamic allocation procedure that is part of iMedidata Rave, known as Balance. After stratification (Fig. 1), patients will be randomized at a 1:1 ratio between:**Arm A:** Pre-op SRS followed by surgery (within two weeks post-SRS).**Arm B:** Surgery followed by post-op SRS (within four weeks of surgery).

**Fig. 1 Fig1:**
[figure not shown]
Study time flow diagram from registration, to randomization, to intervention, to followup

### Radiation fractionation and target dose

The dose prescription is to be delivered in a single SRS fraction. The volume of the metastasis will determine the total prescribed dose. For pre-operative SRS, the contrast enhanced tumor planned for resection is the clinical gross tumor volume (CGTV), and defines the clinical target volume (with an optional 1 mm expansion for dural contact)  (GTV = CTV) (Arm A). For post-operative SRS,  the surgical bed with a 1 mm margin will be used as the CTV (Arm B). 

For GKRS, the dose should be prescribed to the highest isodose line encompassing the clinical target volume (CTV), which can range from 50 to 90% of the maximum dose.

For LINAC-based SRS, the target volume should be prescribed to a planning target volume (PTV) representing a 1 to 2 mm expansion on the CTV. The maximum dose to the target defined as dmax should be a minimum of 125%.

### Radiation therapy dosing:

Lesions < 4.2 ccs receive 20 Gy (22 Gy is allowed for subcentimeter metastases)Lesions ≥ 4.2c to <8.0 cc receive 18GyLesions ≥ 8.0 to <14.4 cc receive 17GyLesions ≥ 14.4 to <20cc receive 15GyLesions ≥ 20 to <30cc receive 14GyLesions ≥ 30cc max 12Gy

### Sample size and power

Statistical considerations regarding sample size and study power are based on the primary endpoint CNS composite endpoint event (CNS-CE). In Mayo Clinic’s experience, the time to CNS-CE for the Sx-SRS group is about six months. Using the log-rank test with a one-sided alpha level of 0.10 a total of 116 evaluable patients (58 in Group A and 58 in Group B) will provide 90% power to detect at least a four-month increase in median time to CNS-CE event from 6.0 months to 10.0 month in Arm B (post-operative SRS) versus Arm A (pre-operative SRS) (EAST 6.4). The final analysis will be conducted when 104 events have occurred; or when all patients are either censored or have been followed for at least 24 months, whichever occurs first. We anticipate accruing an additional 24 patients to account for ineligibility, non-evaluability, and cancellations. This design has a 46.2% chance of stopping early if there is no difference between the treatment groups and only a 2.5% chance if the Sx-SRS group has a greater time to CNS-CE event time than the SRS-Sx group. Note: In this patient population, the expected drop-out rate due to lost-to-follow-up is less than 2%; therefore, most patients are expected to be evaluable for the primary and secondary endpoints.

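### Allocation is balanced on six factors, but the only test named is a log-rank that does not mention them; if the factors are prognostic, a main-effects Cox test would use the data better

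*Protocol article*

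**What the plan says.** The Methodology section of the protocol article lists six stratification factors: age (2 levels), number of brain metastases (3), size of the metastasis to be resected (2), primary malignancy (3), dural contact (2) and radiotherapy modality (2). Of the dynamic allocation it says: "This procedure will balance the marginal distributions of the stratification factors between arms".

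The Sample size and power section names the test and its calibration: "Using the log-rank test with a one-sided alpha level of 0.10 a total of 116 evaluable patients". The arms are of equal size, with 58 patients each, and the stated claim for this number is that it "will provide 90% power to detect at least a four-month increase in median time to CNS-CE event from 6.0 months to 10.0 month". On timing, the section says: "The final analysis will be conducted when 104 events have occurred". A fallback brings the analysis forward if every uncensored patient reaches two years of follow-up sooner.

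The Data management and statistical analysis section gives the intention-to-treat set, two sensitivity analyses and one futility look at 52 events, with a hazard-ratio cut-off of 1.032. It names no primary test and no covariates, and does not say whether the interim hazard ratio is adjusted. The sample-size section gives stopping probabilities of 46.2% and 2.5% for that look.

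**The concern.** Balancing on a prognostic factor makes the arms more alike than chance would. A log-rank that ignores the factor still counts the chance imbalance in its variance, so it rejects too rarely when there is no effect. In addition, if the hazard ratio is constant within factor levels, pooling over patients with different risks pulls the overall effect towards the null. Both mechanisms cost power.

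With 116 evaluable patients and 104 events, the design has little margin above 90%. The six factors are known for every patient at randomisation, so using them needs no new data. The futility rule raises the same question: a cut-off given to three decimals can fall on different sides of an adjusted and an unadjusted estimate from the same data.

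**Working it through.** **1. The plan's own figures.** Inputs from Sample size and power: one-sided alpha 0.10, power 90%, medians 6.0 and 10.0 months, so HR = 6/10 = 0.60 under exponential times; 1:1 allocation.

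- Schoenfeld: 4(1.2816 + 1.2816)² / (ln 0.60)² = 26.28 / 0.2609 = 100.7, so 101 events.
- Freedman: (1.6/0.4)² × (2.5631)² = 105.1, so 106 events. The stated 104 lies between the two.
- Power at 104 events: Φ(0.5108 × √104 / 2 − 1.2816) = Φ(1.323) = 0.907. With the futility look it is 0.899.
- Futility look, standard error of log HR = √(4/52) = 0.277: under HR 1, P(estimate > 1.032) = 1 − Φ(0.0315/0.277) = 45.5% (stated 46.2%); under HR 0.60, 1 − Φ((0.0315 + 0.5108)/0.277) = 2.5% (stated 2.5%).

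The design therefore reproduces as a simple log-rank without covariates.

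**2. Factor structure.** Full cross-classification: 2×3×2×3×2×2 = 144 cells, or 116/144 = 0.8 patients per cell. Main effects: 1+2+1+2+1+1 = 8 terms.

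**3. Effect of ignoring the factors, by simulation.** From the article: N = 116, analysis at 104 events, accrual 31 per year, control median 6 months. Assumed: level shares; exponential times; minimisation with probability 0.8 towards balance; the same hazard ratio on five factors, with radiotherapy modality not prognostic. There is no interim look. With 4,000 trials per scenario, the Monte Carlo standard error near 0.90 is √(0.9 × 0.1/4000) = 0.005. Conditional HR 0.60:

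| Per-factor HR | Log-rank power | Adjusted Cox power | Log-rank size | Adjusted size |
|---|---|---|---|---|
| 1.0 | 0.902 | 0.902 | 0.100 | 0.114 |
| 1.2 | 0.889 | 0.901 | 0.093 | 0.107 |
| 1.5 | 0.855 | 0.900 | 0.081 | 0.108 |
| 2.0 | 0.768 | 0.901 | 0.064 | 0.107 |

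Repeat runs of 2,000 trials with a score test gave 0.86 to 0.87 against 0.90 at HR 1.5, and 0.79 to 0.80 against 0.90 to 0.91 at HR 2.0. The gaps are thus about 1 point at HR 1.2, 3 to 5 at HR 1.5 and 10 to 13 at HR 2.0.

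**4. Dependence on how the effect is defined.**

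- Proportional hazards within factor levels, with the overall arm medians set to exactly 6 and 10 months: log-rank 0.858 and adjusted 0.899 at HR 1.5; 0.781 and 0.898 at HR 2.0.
- Exponential times overall with marginal HR 0.60 (1,200 trials each): log-rank 0.89, 0.91, 0.92 and 0.93 at per-factor HR 1.0, 1.2, 1.5 and 2.0; adjusted 0.95 to 0.97 at HR 1.5 to 2.0. The log-rank keeps its planned power, and adjustment adds 3 to 4 points.

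**5. Two limits on the remedy.** A log-rank stratified on all 144 cells has power of about 0.49 in every scenario of step 3. The adjusted test has size of about 0.11. Moving alpha from 0.10 to 0.11 in the step 1 formula gives Φ(2.605 − 1.227) = 0.916 against 0.907, so about 0.9 points of its apparent gain is size inflation.

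**The case against.** The strongest reply is that the log-rank sentence describes how the trial was sized. Using a simple formula for that is routine and does not fix the final analysis. A reader might infer that the primary test is declared unadjusted, but no such word appears. The article condenses a fuller protocol, and the analysis plan, which is not shown, may well specify covariates. This stands: silence on covariates is not a fault in itself.

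A reader might also infer that the stated 90% is wrong, or holds only if no factor matters. The documents do not support that either. They give population medians, and read as a marginal hazard ratio of 0.60 these leave the log-rank at about 90% even with strong factors. Weak factors cost at most about 1 point on any reading. This also stands, with one reservation: matching the two medians alone does not secure 90% if hazards are proportional within factor levels (step 4).

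Finally, a log-rank after minimisation is valid and errs on the safe side, whereas the adjusted test is slightly liberal at an alpha that is already lenient. At the interim, eight terms plus treatment share 52 events, about 52/9 = 5.8 per parameter. These are real costs and belong in the choice of model. They do not cancel the gain, because under prognostic factors the adjusted test is more powerful on both definitions of the effect, by more than its size inflation explains.

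**Conclusion.** The point holds as an efficiency improvement, not as the correction of an error. The only test the article names takes no account of six factors that it takes care to balance, and its power and futility figures are calibrated without them. If the final analysis follows that wording and the factors are prognostic, the test is conservative and power is given up.

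The amount cannot be derived from the documents, which give no prognostic effect or level share for any factor. The range runs from nothing to about 13 points under a conditional hazard ratio of 0.60. A gain of several points needs a hazard ratio of about 1.5 on each of five factors at once. Under a marginal hazard ratio of 0.60 there is no shortfall, only 3 to 4 points of extra power at per-factor HR 1.5 to 2.0.

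**What to change.** Before the interim analysis, and without sight of comparative data, make these changes:

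- Prespecify as primary the one-sided score or likelihood-ratio test of treatment in a Cox model with the stratification factors as main effects: all eight terms, or a prespecified subset of the main prognostic factors.
- Keep the unadjusted log-rank as a sensitivity analysis.
- State that the log-rank will not be stratified on the full 144-cell cross-classification.
- State which hazard ratio is compared with 1.032 at the interim. If it is the adjusted one, recheck the 46.2% and 2.5% stopping probabilities, and consider the shorter covariate list given only 52 events.

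The cost is wording in the protocol and analysis plan plus a short recheck of operating characteristics; no new data are needed. The Trial status section reports 65 patients enrolled and the interim criteria not yet met at submission, so the change was still possible then. The named downside is a size of about 0.11 against 0.10, which fewer terms or a re-randomisation p-value would address. If the analysis plan already specifies such a model, the only change is to align the article's sample-size and futility wording with it.

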### Data management and statistical analysis

All data will be entered into electronic case report forms (eCRF’s) through the Medidata Rave system. Case report forms will be automatically rolled out based on a predetermined and visit-based schedule to improve study staff workflow and data quality. Data will be exported nightly to a secure FTP for analysis and reporting.

The main objective is to assess whether patients with brain metastases who meet the eligibility criteria experience a longer time until a combined outcome of negative events, such as local recurrence, leptomeningeal disease, or symptomatic radiation brain necrosis, when they undergo SRS before surgery compared to those who undergo surgery before SRS.

Efficacy analysis will be based on the intention-to-treat principle with all eligible patients belonging to the treatment group to which they were randomized. A sensitivity analysis will also be performed based on the treatments received, comparing pre-operative SRS to post-operative SRS. Based on cavity size, a sensitivity analysis will also be performed for patients assigned to post-operative SRS who cannot receive post-operative SRS.

Interim Analysis: One interim futility analysis will be conducted when 50% (52 events) of the CNS-CE events have occurred (approximately 35 months after the study opens). If the hazard ratio comparing Arm A (pre-operative SRS) to Arm B (post-operative SRS is greater than 1.032, we will conclude that the SRS-Sx (pre-operative) treatment is not superior to Sx-SRS (post-operative) and report that the result; otherwise, conclusions will wait until the end of the study.

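### The stated 90% power needs 104 CNS-CE events from 116 patients, but death is not an event and the article states no death rate; under plausible death rates the expected events and the power fall below those stated

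*Protocol article*

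**What the plan says.** Under Sample size and power the article sets the test ("Using the log-rank test with a one-sided alpha level of 0.10"), the effect (an increase in "median time to CNS-CE event from 6.0 months to 10.0 month") and the size: "a total of 116 evaluable patients (58 in Group A and 58 in Group B) will provide 90% power". Allocation is 1:1 (Randomization).

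The same section gives two triggers for the final analysis, the second set at 24 months and the earlier of the two to apply: "The final analysis will be conducted when 104 events have occurred; or when all patients are either censored or have been followed for at least". No power is stated for the second trigger. On attrition it says that "the expected drop-out rate due to lost-to-follow-up is less than 2" per cent, and concludes that most patients will be evaluable. The 24 patients accrued beyond 116 are set aside for those who cancel, prove ineligible or cannot be evaluated; Duration of the project adds major protocol violations. Death is not among these reasons.

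Primary goals defines the event as the first of local recurrence, leptomeningeal disease or symptomatic radionecrosis. Overall survival is a separate secondary goal. Follow-up records death up to five years.

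The futility look, under Data management and statistical analysis, takes place "when 50% (52 events) of the CNS-CE events have occurred (approximately 35 months after the study opens". Duration of the project plans 4.5 years of accrual and 6.5 years in total.

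**The concern.** The target of 104 events is 104/116 = 89.7% of the evaluable patients. Only 12 may die first, be lost or remain event-free. A patient who dies without a CNS-CE can no longer contribute an event, and in a population with brain metastases such deaths are to be expected. The sample-size text mentions no allowance for them.

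If the events do not accrue, the final analysis comes through the 24-month clause with fewer than 104. The stated 90% power then does not describe the test that will be run. The futility rule at 52 events would also be applied later in the trial's information than the stated half.

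**Working it through.** **Inputs from the article.** One-sided alpha 0.10; medians 6 and 10 months, so HR = 6/10 = 0.60 under exponential times; 58 patients per arm; accrual 54 months; total duration 78 months; final target 104 events; interim at 52.

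**Input not in the article.** The death hazard among patients still free of CNS-CE. I take exponential medians of 36, 24, 18 and 12 months, with uniform accrual, death censoring the CNS-CE time, and no loss to follow-up.

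**Step 1: the plan's own figure, events to power.** Schoenfeld events = 4 × (1.2816 + 1.2816)² / (ln 0.6)² = 100.7, so 101. Power at D events = Φ(½√D × |ln 0.6| − 1.2816). At D = 104: 5.099 × 0.5108 − 1.2816 = 1.323, giving 90.7%, or 89.9% after the power lost to the futility rule. This step reproduces.

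**Step 2: patients to events without deaths.** With event hazard λ = ln 2/median and death hazard δ, the expected events by month 78 are the sum over the two arms of

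58 × λ/(λ+δ) × [1 − (e^(−24(λ+δ)) − e^(−78(λ+δ))) / (54(λ+δ))].

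With δ = 0: 58 × 0.9900 + 58 × 0.9506 = 57.4 + 55.1 = 112.6 before rounding of the parts. So 104 is reachable if nobody dies first.

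**Step 3: the same with deaths.** Example, death median 24 months: δ = 0.02888.
- Post-operative arm: λ = 0.11552; 0.8000 × 0.9960 = 0.7968; 46.2 events.
- Pre-operative arm: λ = 0.06931; 0.7059 × 0.9822 = 0.6933; 40.2 events.
- Total 86.4; power = Φ(½√86.4 × 0.5108 − 1.2816) = Φ(1.09) = 86.3%.

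The time of the 52nd event solves Σ (58/54) ∫₀ᵀ λ/(λ+δ) × (1 − e^(−(λ+δ)t)) dt = 52.

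| Death median without CNS-CE (assumed) | Events from 116 | Power | 52 as share of expected events | Month of 52nd event |
|---|---|---|---|---|
| 36 months | 93.7 | 88.3% | 55% | 38.6 |
| 24 months | 86.4 | 86.3% | 60% | 40.5 |
| 18 months | 80.2 | 84.3% | 65% | 42.5 |
| 12 months | 70.0 | 80.4% | 74% | 46.6 |

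A log-rank simulation (4,000 runs per row, futility rule included) gave power of 87.3, 85.1, 83.4 and 80.1% for the four rows. It reached 104 events in 0.6% of runs at 36 months and in none at 24 months or less.

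**Step 4: break-even.** Setting expected events to 104 gives a death median of about 88 months. Setting them to the 101 that Schoenfeld requires gives about 63 months.

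**Step 5: upper bound with all 140 accrued patients.** Scaling by 140/116 gives 104.3, 96.8 and 84.5 events at 24, 18 and 12 months, and power of 91, 89 and 86%.

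**The case against.** The strongest reply is that nothing is miscalculated. Given 104 events, 90% power is right. The article condenses a fuller protocol in which the software inputs and censoring rules may be set out, and the second trigger shows that the authors foresaw a shortfall. The size of the loss rests on a death rate that the documents do not give. It is also small at the longer medians. All of that stands. What it does not rescue is the statement itself: the article ties 90% power to 116 evaluable patients and 104 events, and discusses attrition in terms of loss to follow-up alone.

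A reader might infer that the 35-month interim date proves a projection with no deaths. It does fit 116 patients over 54 months without deaths (35.0 months). It fits equally well with deaths at a 24-month median if 140 patients enter over 54 months (34.9 months, with 104.3 events by month 78). The same holds if 116 enter at the stated 31 eligible per year, which takes about 45 months (35.1 months). The date does not settle what was modelled.

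A reader might also set the 6-month control median, which implies 75% with an event at one year, against the background statement that "28% of patients undergoing post-operative SRS after resectioning of one, two, or three metastases recurred locally within one year". The two do not conflict. The second is one component of the composite, from a cited study of one to three resected metastases; the first is institutional experience with a three-part composite.

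Finally, not every death matters. Deaths after a CNS-CE cost no events, so an overall-survival median put into this calculation could overstate the loss. The relevant rate is death among patients still free of CNS-CE.

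**Conclusion.** The point holds as a fault in the projection from patients to events, not in the step from events to power. The expected count falls below 104 for any event-free death median under about 88 months. That direction does not depend on the exact rate; the size does. For medians of 36 to 12 months the stated 90% becomes about 88 to 80%, a loss of roughly 2 to 10 points, and the interim falls at about 55 to 74% of expected events.

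This rests on exponential times, uniform 54-month accrual, analysis at month 78, independent censoring by death and HR 0.60. The article does not say how deaths entered its 6- and 10-month medians; I have read them as event times with deaths censored.

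It would go too far to call the trial badly underpowered, or to say that the article shows deaths were ignored. It shows only that no allowance for them is stated and that 116 patients are unlikely to deliver 104 events.

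**What to change.** In Sample size and power, state that death before a CNS-CE is not an event and how it is handled. Give the assumed death rate among event-free patients beside the loss-to-follow-up figure. Re-project the events from 116 evaluable patients on that basis and state the power at the expected count, including for a final analysis triggered by the 24-month clause.

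In the interim analysis paragraph, restate 52 events as a fraction of the expected events and revise the 35-month timing to match.

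Keep any eligible patients beyond 116 in the intention-to-treat analysis. Quote the 140-patient figures only as an upper bound: the extra 24 are there to absorb other losses, and the efficacy analysis is of eligible patients.

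The cost is a recalculation, some wording and a less favourable stated power. No extra patients are needed to make the correction. At submission 65 patients were enrolled and the interim criteria had not been met, so it could still be made before any look at the data.
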